## 9.2 Doses and mode of vaccine delivery

All DNA/Placebo immunizations will be performed with a Biojector device according to the manufacturer's instruction. Intradermal (i.d.) injections will be given in the skin over the deltoid muscle with the extension supplied by the manufacturer for this purpose. The DNA injection of 0.1 ml is performed at a concentration of 3mg/ml in Groups I and II, and 2 mg/ml in Group III. The MVA-boost injection will be delivered intramuscularly in the deltoid muscle.

## 9.3 Vaccination procedures and safety follow-up after immunization

The immunizations will take place in an outpatient setting. Participants will receive a baseline medical status check up including vital signs assessment to confirm on the medical eligibility before vaccine administration. Results will be documented in the appropriate CRF forms (**CRF 3-II, CRF 10-I**). Safety lab procedures, urine analysis as well as HIV testing will be performed before vaccine administration according to the visit schedule. A pregnancy test for female participants before each vaccination will have to show negative results vaccination. The pregnancy test for female participants before each vaccination will have to show negative results *before* vaccination. A vaccine request form (**CRF 10-II**) indicating the study visit number, the site and participant code, the date as well as the immunization number and immunization Group will be filled then by the study medical officer and transferred to the study pharmacist, who will deliver to the nurse the appropriate vaccine/placebo corresponding to the assigned study group. After each immunization participants will be closely observed at the clinic for 30 minutes. Vital signs and any local or systemic reaction will then be recorded and participants will be seen briefly by the medical officer to document the post vaccination status (**CRF 3-II, CRF 10-I** - this record will be indicated in the CRF with the visit number plus A). The needles, syringes and other materials will be disposed according to MNH /MMRP biohazard regulations. As with any parenteral vaccine, epinephrine and corticosteroids will be available for immediate use should an immediate hypersensitivity reaction, such as anaphylaxis, occur. Intravenous injections of vaccines will NOT be performed. Study vaccine will not be administered to individuals with hypersensitivity to any component of the vaccine. All immediate hypersensitivity reactions will be managed according to the developed SOP's. Volunteers will be contacted by phone, home visit or clinical contact at the first day following immunization for a brief adverse reaction interview. Additionally, volunteers will complete diaries over events for the evening of the vaccination day and the 7 days following each vaccination. A diary card (*see Appendix 8*) will be provided after each vaccination schedule, with instructions and a full verbal explanation for volunteers to record local and systemic adverse events following immunization, as well as any medication taken. A folder with diary cards, disposable thermometers and a ruler will be issued to each volunteer. The clinical team will provide contact information as well as a telephone numbers to call 24 hours, in order to assure contact with the study personnel if needed.

All volunteers will be asked to contact the study site in the case of adverse events of suspected grade 2 or more for evaluation. A decision to offer the volunteer a visit to the clinic should be made and documented in the source documents. All volunteers with suspected grade 3 or more should be seen by the study physician and documented in the source documents.

Additional visits may be recommended at the discretion of the clinical and principal investigators, if clinically indicated or in order to clarify observations.

Safety follow-up visits are scheduled at week 2 and week 4 after each immunization visit. Diary cards will be reviewed and discussed latest at the scheduled 2 weeks follow-up visit after each vaccination. Diary entries will be transcribed after revision and discussion with the participant during the follow up visits after each vaccination into the Vaccine/Reaction Form (**CRF 10-I**). All concomitant medication must be recorded in study form **CRF 4-I** with the

reason for administration, the dosage regimen, the onset and end of treatment. All medical conditions (symptoms and/or diagnosis) that are not defined and indicated in the vaccine reaction form (**CRF 10-1**) will be recorded in the adverse events form (**CRF 6-I**) including the severity grade and the relationship to the study agent. Each of the 7 recording days will be recorded as a visit (**CRF 2-II**) with the visit number of the respected vaccination visit together with a capital letter indicating the recording day for adverse reaction (B for day 1, C for day 2, etc.).

The need for the following medications will lead to study discontinuation

- Immunomodulatory agents (i.e. immunoglobulin)
- Immunosuppressive agents (i.e., systemic steroids, chemotherapy)
- Live, attenuated vaccines. Other vaccines (subunit or killed) should be given at least two weeks before or two weeks after HIV immunization.

## 10 THE VACCINE (TRIAL PRODUCTS)

### 10.1 DNA Priming

Will be effected with DNA plasmids derived from plasmid puC8 and carrying a kanamycin resistance gene, promoter from human cytomegalovirus (hCMV), poly A signal from Human Papilloma Virus 16 and origin of replication for *E. coli*. The plasmids will be carrying HIV-1 genes of subtypes A, B and C. These are pKCMV**gp160A**, pKCMV**gp160B**, pKCMV**gp160C**, pKCMV**rev**, pKCMV**p37A(ba)**, pKCMV**p37B**, and pKCMV**RTB**.

The primary envelope gene is that of subtype B. This gene was used for homologous recombination to obtain variable sites of subtypes A and C. Thus the most variable regions of gp120 from subtypes other than the primary could be included, and the most conserved proteins conserved in the vaccine mixture [44-46].

#### Supply, storage and composition of DNA

Vecura Company (Karolinska University Hospital at Huddinge, Stockholm, Sweden) will be responsible for bulk manufacture of the DNA vaccine, release testing and technical release of vialled product and labeling. All procedures will be according to Good Manufacturing Practice. The presentation is in liquid form at either 2 or 3 mg per mL, which should be stored at -20 °C until use. Care will be taken not to break the cold chain.

The DNA plasmids were approved for human use on November 27th 2004 by the Swedish Medical Products Agency, (Svenska Läkemedelsverket), and the second revision of the protocol ethically cleared by the Swedish Internal Review board, (Regionala forskningsetiska kommittén) in December 2004. The new batch of the same plasmids will need to have a further approval by the Tanzania Food and Drugs Authority (TFDA).

Sterile commercially available normal saline for human use will be used as the placebo.

#### Labels

DNA will be packaged by Vecura. The trial products will be in vials pre-labeled according to standardized operating procedures. Each vial will be packed in a box labeled with the name of the clinical site and principal investigator, the storage details and the name of the supplier of the product, the name of the manufacturer, as well as the manufacture and expiry dates. The labels should also have the caption "for clinical trial only".

Cartons will be supplied to the designated pharmacist at MUHAS and NIMR-MMRP for storing the used vials, labeled with the supplier, the name of the trial and protocol version, the name of the clinical site and principal investigator and the content of the material (DNA vaccine or placebo).

Having been manufactured by Vecura Company, the DNA vaccine will be supplied to the study by the Swedish Institute for Infectious Disease Control, [name]. SWEDEN.

Prior to use the vials will be thawed at room temperature. Thawed vials will then gently be swirled. Care will be taken not to shake or invert the vials.

## **10.2 MVA Boosting**

Boosting will be effected by a Modified Vaccinia Ankara vaccine (MVA-CMDR). The MVA - CMDR, produced by WRAIR/NIH, is a live recombinant poxvirus vector vaccine that has been genetically engineered to express the following HIV-1 genes:

1. **gp150** (Subtype E, CM235), and
2. **gag** and **pol** (integrase-deleted and reverse transcriptase nonfunctional, Subtype A, CM240).

MVA-CMDR is formulated in a liquid form in vials and will be administered at a dose of  $10^8$  pfu by intramuscular route following appropriate dilutions.

### Supply, storage and composition of MVA

Walter Reed Army Institute of Research (WRAIR), USA, will be responsible for the bulk manufacture of the clinical material, release testing, as well as the technical release of vialled product, and labeling. The full address of the manufacturer is: *Walter Reed Army Institute of Research (WRAIR), [name], Department of Biologics Research The Pilot Bioproduction Facility, [name] 20910, USA*. All procedures will be according to Good Manufacturing Practice. The presentation is in liquid form at  $10^8$  pfu per mL with an extractable volume of 1ml vials, which should be stored at  $-20^{\circ}\text{C}$  up to 3 months ( $-80^{\circ}\text{C}$  if longer than 3 months) until use. Care should be taken not to break the cold chain. The product has already received approval from the USA Food and Drugs Authority (FDA), and the Swedish Medical Products Agency and will be presented to the TFDA for approval before use in Tanzania.

Sterile commercially available normal saline for human use will be used as the placebo.

### Labeling

Each vial will be packed in a box labeled with the name of the clinical site and principal investigator, the storage details and the name of the supplier of the product, the name of the manufacturer, as well as the manufacture and expiry dates. The labels should also have the caption "for clinical trial only".

### Measures to ensure cold-chain maintenance and storage.

Cold chain will be maintained by transportation packages according to manufacturer's instruction during shipment. The packing at Sweden will be divided into two different parcels (one parcel for each site) to avoid re-opening the parcel before transporting to Mbeya site. The storage facilities have automatic backup generators to maintain storage temperature. At Dar es Salaam site, transport of the investigational product from microbiology laboratory to clinic site will be done using study van in a container packed with ice bags. At the MMRP site investigational products will immediately be transferred and stored into the existing freezer at

the MMRP pharmacy. The study pharmacy and study clinic are located on the same ground within the same building.

#### Transportation to the Mbeya Site

The Pharmacist at Dar es Salaam site will be responsible for transporting the investigational products allocated to Mbeya site after being handled to him/her by world courier at Dar es Salaam Airport. In the same day, the investigational products will be transported using study van to Mbeya site. Investigational products allocated to Mbeya site will be transported into their original packaging containers without opening at Dar es Salaam site. The pharmacist at Mbeya site will receive the products handled to him/her by filling the handling documents before storing into the respective storage temperatures.

### **10.3 Dispensing records and disposal of unused product**

The designated pharmacist will, upon receipt of supplies prior to commencement of the trial, conduct an inventory and complete a receipt, one copy of which will be retained at the site, and the original returned to the supplier (Karolinska Institute, Sweden). During the trial the pharmacist will be responsible for reviewing the dispensing log. On the day of immunization the study nurse will fill in the vaccine request form with the study visit number, the site and participant code, the date as well as the immunization number and immunization Group (2x versus 5x i.d. DNA priming). Upon receipt of the syringes with the vaccine from the pharmacist, the study nurse will deliver the vaccine. The immunization number and date will be entered against the study number in the dispensing log. The vial label will be cross-checked against the details on the vaccine request form and dispensing log by two individuals (pharmacist and nurse), prior to the vaccine/placebo being administered.

The Pharmacist will be responsible for ensuring that the return of used vials is recorded in the dispensing log at the end of the clinical session, and that they are placed in the appropriate volunteer carton. At the end of the trial all used and unused vials will be checked against the inventory by the monitor before disposal on site according to MNH/MMRP biohazard regulations. Documentation of disposal will be provided to the monitor and supplier. During the trial, product accountability will be monitored by the vaccine request form, the dispensing log, the returns, the trial register and data collected on the clinical research forms.

## **11 ENDPOINTS**

### **11.1 Safety**

The safety of immunization with the seven DNA plasmids carrying HIV-1 genes and the MVA will be assessed by clinical features as well as standard biochemical and hematological laboratory tests. Any worsening of the severity grade will be considered for causality with the vaccine.

Safety endpoints: Adverse events will be assessed using a standard format for soliciting local and systemic reactogenicity to the vaccine and collection of unsolicited adverse events. Solicited reactogenicity will be evaluated for 7 days following each vaccination. All other AE will be collected from the time of first injection until 3 months after the last injection.

The primary safety parameters will be graded according to the DAIDS Table for Clinical and Lab Criteria for Definitions (*see Appendix 9*) and are:

1. Local adverse event Grade 3 or above (pain, cutaneous reactions including indurations)
2. Systemic adverse event Grade 3 or above (fever, chills, headache, nausea, malaise, myalgia, and arthralgia)

3. Other clinical and laboratory adverse event Grade 3 or above confirmed at examination or on repeat testing respectively

The relationship to the vaccine should be evaluated as:

- 1= not related
- 2= probably not related
- 3= possibly related
- 4= probably related
- 5= definitely related

Tests for possible toxicity due to vaccination will include: Liver function tests, renal function tests and complete blood count and differential with platelets. Any event attributable to vaccine leading to discontinuation of the immunization regimen must be documented.

Data on local and systemic events listed above will be solicited with specific questions or using a diary card for a minimum of 7 days following each immunization. Data on other clinical events and laboratory events will be collected with an open question at each visit and through routine scheduled investigations respectively.

### 11.2 Immunogenicity

HIV-specific cellular and humoral immune responses will be assessed.

#### *Primary endpoint*

The primary immunogenicity endpoint will be assessed at the trial sites by the IFN- $\gamma$  ELISPOT assay using fresh cells.

#### *Secondary endpoints*

Intracellular cytokine staining quantifying IFN- $\gamma$  and IL-2 production by CD4 and CD8 T-cells and lymphoproliferation against inactivated HIV using fresh cells.

Multi-color intracellular cytokine staining using cryopreserved cells for assessment of multiple T-cell effector functions including immunophenotyping of responding cells.

Binding (and if present, also neutralizing) antibodies.

## 12 SAFETY AND IMMUNOGENICITY ASSESSMENTS

### 12.1 Safety assessment

Local and systemic assessments whether normal or abnormal will be recorded starting from 30 minutes up to 4 weeks after immunization in the following intervals: 30 minutes as direct observation after immunization, at the evening of the vaccination day and at days 1-7 as recorded by diary cards by the participants with clinic or home visit if indicated, plus follow-up safety visits 2 weeks and 4 weeks after each immunization. While study personnel will use the vaccine/reaction form (**CRF 10-I**) to record all local and systemic events at the clinic, participants will use diary cards at home for the same. On the Adverse Events Form (**CRF 6-I**) all medical events throughout the entire study period will be reported, excluding those local or systemic reactions indicated on the Vaccine/Reaction Form (**CRF 10-I**) during the first 7 days post vaccination. The study site will contact participants at the first day after vaccination for an adverse events/reaction interview. Participants will be instructed to call or report to the specified study personnel immediately if any unusual or severe sign or symptom appears after immunization. Participants with suspected grade 3 or above events should be seen in the clinic at the time of maximal symptoms, if possible, and will be followed up clinically until resolution of symptoms.

An adverse event is any undesired, noxious or pathological change in a participant as indicated by physical signs, symptoms, and/or laboratory changes that occurs following administration of one of the vaccines, whether or not considered vaccine related. This definition includes intercurrent illnesses or injuries, and exacerbation of pre-existing conditions.

#### **12.1.1 Local adverse events**

Pain at the injection site will be graded by the volunteer according to the criteria in the DAIDS Table for Clinical and Lab Criteria for Definitions (**see Appendix 9**) as mild (1) moderate (2), severe (3) or serious/life threatening (4) and recorded in the appropriate case record form. In the diary card grading will refer only to mild (1) moderate (2) and severe (3) as the distinction between severe and serious should be made in association with the medical officer after having reported to the clinic once the volunteer has left clinic. Swelling, redness and indurations will be recorded as the maximum diameter as well as the presence of any itching or other discomfort and any medication taken for relief of symptoms. Blistering (vesiculation) or ulceration will be graded according to size, depth, time to healing and character of blisters (blood-filled).

Clinical staff will complete the case record form following each immunization. In the event that there are two observations on the same day, those confirmed at a visit will take precedence over diary card observations in the analysis. Study personnel should verify all grade 3 or 4 events.

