## 9 IMMUNIZATION

### 9.1 Immunization schedule

While DNA/Placebo immunizations will be performed at weeks 0, 4 and 12, MVA/Placebo will be given at weeks 30 and 46. The immunization schedule is summarized below:

| Study week                                              |    | 0                                                                                                             | 4                                                                                                                 | 12                                                                                                                 | 30                                                              | 46                                                               |
|---------------------------------------------------------|----|---------------------------------------------------------------------------------------------------------------|-------------------------------------------------------------------------------------------------------------------|--------------------------------------------------------------------------------------------------------------------|-----------------------------------------------------------------|------------------------------------------------------------------|
| Injection schedule in days
+/- acceptable time frame |    | 0                                                                                                             | 28 days (+/-3)
post DNA I                                                                                      | 84 days (+/- 7)
post DNA I                                                                                      | 126 days post V8 +14 /-28
days                               | 112 days post V11
+14 /-28 days                               |
| Study Group                                             | N  | 1 st vaccination                                                                                   | 2 nd vaccination                                                                                       | 3 rd vaccination                                                                                        | 4 th vaccination                                     | 5 th vaccination                                      |

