#### **12.1.2 Systemic adverse events**

Temperature will be measured by the axillary route prior to immunization and 30 minutes after the immunization by study personnel and graded according to the DAIDS Table for Clinical and Lab Criteria for Definitions. Participants will be given thermometers to record their temperature in the diary card on the evening of immunization, and daily thereafter for 7 days, and if still raised, they will be advised to continue to monitor their temperature daily until it returns to normal. The temperature observed by the clinical team will be recorded in the case record forms for visits. In case of grade 3 and 4 fever, malaise, chills/rigors and headache, and where indicated, additional tests to exclude other common causes of fever like malaria will be performed.

Chills, headache, nausea, malaise, myalgia, and arthralgia will be graded by the participants according to mild, moderate or severe impression and recorded in the diary card on the evening following immunization and daily for 7 days, or until resolution of symptoms whichever is longer. At the next study clinic visit diary entries will be reviewed and discussed by the medical officer with the participants and events will be transferred into the case report form according to the DAIDS Table for Clinical and Lab Criteria for Definitions. Data entry in the CRF will take precedence over diary card entries in the analysis. Study personnel will verify all grade 3 or 4 events.

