**Appendix 1: Study Timetable**

| Target day | Week | Visit | Visit purpose                                  | Visit Window                   |
|------------|------|-------|------------------------------------------------|--------------------------------|
|            | -4-8 | V1    | Screening I                                    | 4-8 weeks before V3 enrolment  |
|            | -2-4 | V2    | Screening II + baseline immunogenicity I       | 2-4 weeks before V3 enrolment  |
| 0          | 0    | V3    | Enrolment + DNA I + baseline immunogenicity II | Week 0                         |
| 0          |      | V3A   | 30 min post vaccination                        |                                |
| 0          |      | V3B   | Evening of vaccination day                     |                                |
| 1          |      | V3C   | Day 1 post vaccination                         |                                |
| 2          |      | V3D   | Day 2 post vaccination                         |                                |
| 3          |      | V3E   | Day 3 post vaccination                         |                                |
| 4          |      | V3F   | Day 4 post vaccination                         |                                |
| 5          |      | V3G   | Day 5 post vaccination                         |                                |
| 6          |      | V3H   | Day 6 post vaccination                         |                                |
| 7          |      | V3I   | Day 7 post vaccination                         |                                |
| 14         | 2    | V4    | Follow-up safety (+ immunogenicity)            | 14 days post V3 +/- 3 days     |
| 28         | 4    | V5    | DNA II + Follow-up safety                      | 28 days post V3 +/- 3 days     |
| 28         |      | V5A   | 30 min post vaccination                        |                                |
| 28         |      | V5B   | Evening of vaccination day                     |                                |
| 29         |      | V5C   | Day 1 post vaccination                         |                                |
| 30         |      | V5D   | Day 2 post vaccination                         |                                |
| 31         |      | V5E   | Day 3 post vaccination                         |                                |
| 32         |      | V5F   | Day 4 post vaccination                         |                                |

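### Read literally, the same-day precedence rule in 12.1.1 lets the 30-minute clinic finding displace the evening diary entry for local reactions on each vaccination day

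*Protocol*

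**What the plan says.** For local reactions, Protocol 12.1.1 states that, given "two observations on the same day, those confirmed at a visit will take precedence over diary card observations in the analysis". It makes no exception for the day of injection.

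Protocol 12.1 sets the observation times as "30 minutes as direct observation after immunization, at the evening of the vaccination day and at days 1-7 as recorded by diary cards", and requires normal as well as abnormal findings to be recorded. Section 9.3 confirms that the 30-minute check is a staff record: "Vital signs and any local or systemic reaction will then be recorded and participants will be seen briefly by the medical officer". The same section says "volunteers will complete diaries over events for the evening of the vaccination day and the 7 days following each vaccination".

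For systemic reactions, 12.1.2 has a different rule: "Data entry in the CRF will take precedence over diary card entries in the analysis". The sentence before it has the medical officer review the diary and move its events into the case report form.

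The record labels disagree. Section 9.3 gives the 30-minute record the letter A and the diary days "B for day 1, C for day 2, etc". Appendix 1 gives A to the 30-minute check, B to the "Evening of vaccination day" and C to day 1.

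**The concern.** A rule that prefers clinic findings to self-report makes sense when both describe the same reaction at the same time. On a vaccination day they do not: the clinic observation comes half an hour after injection and the diary entry comes hours later. A normal arm at 30 minutes is a recorded visit observation, and under the literal rule it takes precedence over pain or induration noted that evening. Where the two differ because a reaction has developed in between, the rule can only lower the analysed grade.

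Local events of grade 3 or above are a primary safety parameter (11.1). Local reactions within 7 days are also part of the stated comparison of two against five intradermal injections (20.1). Under-recording of short-lived evening reactions would make both look milder than they were.

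**Working it through.** The plan gives no figure on this point, so there is none to reproduce. The check sets the passages together, counts the exposed entries, and illustrates the possible loss with assumed rates.

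**1. Does the rule reach the vaccination day?** 12.1.1 applies whenever two observations fall on one day. 12.1 and 9.3 schedule exactly two on each vaccination day, one by staff and one by diary. The literal answer is yes.

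**2. How many diary entries are exposed?**
- Vaccination days: 5, from 9.1 ("While DNA/Placebo immunizations will be performed at weeks 0, 4 and 12, MVA/Placebo will be given at weeks 30 and 46").
- Diary entries per vaccination: 1 evening + 7 daily = 8 (9.3).
- Entries per participant: 5 × 8 = 40, of which 5 are evening entries. 5 / 40 = 12.5%.
- Trial total, if all 120 volunteers complete every dose: 120 × 5 = 600 evening entries out of 120 × 40 = 4,800.

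The other 35 entries per participant (days 1 to 7) are touched only if a visit happens on that day.

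**3. When is a local reaction actually lost?** All three conditions must hold:
- it starts, or reaches its worst grade, after the 30-minute check;
- it has eased below that grade by the day-1 diary entry;
- it was not confirmed at an extra visit.

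**4. What could that do to a count?** The documents do not give the share of reactions meeting these conditions, so every input here except 36 per vaccine arm and 5 doses is an assumption. Let r be the true rate per dose of a local reaction of the grade counted, and f the share of those reactions that is lost. With doses taken as independent:

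- true number of participants with an event = 36 × [1 − (1 − r)^5]
- recorded number = 36 × [1 − (1 − r(1 − f))^5]

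| assumed r | f = 0 | f = 10% | f = 50% |
|---|---|---|---|
| 1% | 1.8 | 1.6 | 0.9 |
| 5% | 8.1 | 7.4 | 4.3 |

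For example, at r = 5% and f = 50%: 36 × [1 − 0.975^5] = 36 × 0.119 = 4.3, against 36 × [1 − 0.95^5] = 36 × 0.226 = 8.1.

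**5. Visit letters.** Under 9.3 the sequence is A = 30 minutes, B = day 1, through to H = day 7, so the evening entry has no letter. Under Appendix 1 it is A = 30 minutes, B = evening, C = day 1, through to I = day 7. The letter B therefore denotes two different days in the same protocol.

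**The case against.** The best defence is that 12.1.1 was never meant for the vaccination day. Its wording is conditional, whereas two observations on that day are certain. It fits the unscheduled clinic or home visits that 12.1 allows during the diary days better. A finding made before a reaction began cannot be said to confirm anything about it. Diary entries are also reviewed at the follow-up visit and transcribed into the vaccine reaction form (9.3), so a reviewed entry might itself count as confirmed at a visit. Appendix 1 lists the 30-minute and evening records separately. This reading is possible, and it makes overwriting a risk of the wording, not a certain outcome. But the protocol does not state it, and the conflicting letters in 9.3 weaken any reliance on a separate evening record.

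A second defence is that derivation of grades belongs in a statistical analysis plan, which is not shown and may settle the matter. Here, though, the protocol itself fixes the rule, and a plan that took the worst grade of the day would depart from its literal text. Section 20.4 does not resolve it either, since it allows counting by worst severity or by first report.

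Three stronger readings are tempting, and the documents do not support them:

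- **Systemic reactions are lost too.** A reader might infer this from the precedence sentence in 12.1.2. That rule ranks the case report form above the diary, after diary events have been moved into the form. It contains no same-day visit rule.
- **Reactions that start hours after injection drop out in general.** Any that still hold their grade on day 1 are captured by the diary for days 1 to 7.
- **The primary grade 3 results are plainly biased.** Volunteers are asked to contact the site for suspected grade 2 or more, and suspected grade 3 or more should be seen by the study physician (9.3), at the time of maximal symptoms where feasible (12.1). Staff are to verify grade 3 and 4 events (12.1.1). A same-day visit would then supply the confirmed observation. This protection is partial, because attendance at the peak is not guaranteed and verification does not change which record ranks first.

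**Conclusion.** The point stands in limited form. As worded, 12.1.1 lets an earlier clinic finding outrank a later and worse local diary entry on every vaccination day. Up to 5 of 40 diary entries per participant (12.5%) are exposed, which is a count of entries at risk and not of events lost. The resulting bias in local reactogenicity is downward and arises only for the short-lived evening reactions described above.

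Its size is unknown. The illustrated range rests on assumed rates and on independence between doses. For grade 3 or higher the low end is the more plausible: sections 4.5 and 4.6.1 report no related grade 3 or 4 events in the Swedish trial and none probably or definitely related in HIVIS 03. The larger exposure is therefore in grade 1 and 2 local reactions. A reader might also infer that the more reactogenic regimen would lose more events and the contrast between regimens would shrink. That would follow only if one regimen has more evening-only reactions, and the documents give no data on this.

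The letter mismatch between 9.3 and Appendix 1 is certain but clerical. It does not decide which grade is analysed, but it can misplace or orphan the evening record.

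**What to change.** In 12.1.1, limit visit precedence to observations of the same reaction at the same time point. State that the 30-minute (VxA) and evening (VxB) records are separate and both retained. For the incidence analysis of local reactions, specify the worst grade over days 0 to 7, and amend 20.4 so that the choice between worst severity and first report is no longer open.

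Separately, reconcile the visit letters in 9.3 with Appendix 1 so that the evening entry has its own letter in both places.

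The cost is protocol wording only, as all the data are already collected. Reported local reactogenicity rates may be slightly higher as a result.
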